## Abstract

**Background:**

Knee Osteoarthritis (KOA) is a major cause of pain and functional impairment among elders. Currently, there are neither feasible preventive intervention strategies nor effective medical remedies for the management of KOA. Tai Chi, an ancient Chinese mind-body exercise that is reported to enhance muscle function, balance and flexibility, and to reduce pain, depression and anxiety, may safely and effectively be used to treat KOA. However, current evidence is inconclusive. Our study examines the effects of a 12-week Tai Chi program compared with an attention control (wellness education and stretching) on pain, functional capacity, psychosocial variables, joint proprioception and health status in elderly people with KOA. The study will be completed by July 2009.

**Methods/Design:**

Forty eligible patients, age > 55 yr, BMI ≤ 40 kg/m^2 ^with tibiofemoral osteoarthritis (American College of Rheumatology criteria) are identified and randomly allocated to either Tai Chi (10 modified forms from classical Yang style Tai Chi) or attention control (wellness education and stretching). The 60-minute intervention sessions take place twice weekly for 12 weeks. The study is conducted at an urban tertiary medical center in Boston, Massachusetts. The primary outcome measure is the Western Ontario and McMaster Universities (WOMAC) pain subscale at 12 weeks. Secondary outcomes include weekly WOMAC pain, function and stiffness scores, patient and physician global assessments, lower-extremity function, knee proprioception, depression, self-efficacy, social support, health-related quality of life, adherence and occurrence of adverse events after 12, 24 and 48 weeks.

**Discussion:**

In this article, we present the challenges of designing a randomized controlled trial with long-term follow up. The challenges encountered in this design are: strategies for recruitment, avoidance of selection bias, the actual practice of Tai Chi, and the maximization of adherence/follow-up while conducting the clinical trial for the evaluation of the effectiveness of Tai Chi on KOA.

**Trial registration:**

ClinicalTrials.gov identifier: NCT00362453

## Background

Knee osteoarthritis (KOA) is a growing problem in the elderly, resulting in pain, functional limitations, disability and decreased quality of life leading to lost productivity and increased health care costs [1,2]. The pathophysiological basis of KOA is multifaceted and includes intra-articular inflammation and collagen degradation, impaired muscle function, reduced proprioceptive acuity and the psychological traits of chronic pain [3-6]. Currently, there are neither feasible preventive intervention strategies nor effective medical remedies for the management of KOA.

Over the past 2 decades, Tai Chi, a form of mind-body therapy, has spread worldwide for health and fitness [7]. Tai Chi combines deep diaphragmatic breathing and relaxation with many fundamental postures that flow imperceptibly and smoothly from one to the other through slow, gentle, graceful movements. Significant improvements have been reported in balance, strength, flexibility, cardiovascular and respiratory function, and reduction of pain, depression, anxiety and arthritic symptoms in a variety of patient populations including KOA [8].

Thus, Tai Chi has the potential to become a novel, logistically feasible way of providing standardized exercises with a complementary mind-body approach to the management of KOA. The physical component provides exercise that is consistent with recommendations for OA (range of motion, flexibility, muscle conditioning, and aerobic cardiovascular exercise) [9], while the mind component has the potential to increase psychological well-being, life satisfaction, and perceptions of health [10]. These effects are especially pertinent for the treatment of older adults who have OA with knee pain and poor physical function.

To date, only five randomized controlled trials (RCTs) conducted between 2000 and 2007 have compared the effect of Tai Chi with various controls in patients with OA [11-15]. The results of three RCTs suggested significant pain reduction compared to controls [11-13], but the other two found no significant changes [14,15]. Significant improvements in physical function were also reported in three RCTs compared with controls [11,13,14], but no effects were seen in the other two [12,15]. Of the two RCTs [14,15] that evaluated the effects of Tai Chi on quality of life, only one reported positive results for Tai Chi compared with controls [15]. In addition, only two RCTs reported significant differences between Tai Chi and control in improvements in flexibility or balance [11,13]. Heterogeneity of controls, different Tai Chi styles, doses and duration in addition to multiple OA sites prohibit a meaningful comparison across these trials. Furthermore, the absence of radiographic evidence of KOA as specified by the ACR criteria for OA [14], high dropout rates [13,14], small sample size [11-13,15], the lack of standardized outcome measures and short follow up [11-15] limit widespread applicability of the results from these studies.

Because the overall findings from these RCTs suggest some favorable effects of Tai Chi on pain, physical function, quality of life, balance and flexibility in patients with KOA, a well designed study may be able to overcome the limitations of the previous studies and provide a more useful treatment. We hypothesize that Tai Chi may be beneficial to patients with KOA as a result of an effect on muscle strength, flexibility, pain, stress and anxiety as well as "mind-body" interactions. We therefore designed a 12 week trial with long term 1 year follow up to obtain data on the effects of Tai Chi on pain (as a marker of disease activity), functional independence (a marker of impairment), disability, joint proprioception and health status in elderly people with KOA.

In this paper, we present the design and detailed protocol of a single-blinded, randomized controlled trial as well as a discussion of the overall challenges of conducting this trial with respect to strategies for recruitment, avoidance of selection bias, the actual practice of Tai Chi, and the maximization of adherence/follow-up. We report ways to overcome the theoretical and logistic limitations and problems of conducting such a clinical trial. The results from this trial will be reported at the completion of the study in accordance with the Consolidation of Standards for Reporting Trials guidelines [16].

## Methods/Design

### Study design

This study is a single-blinded, randomized, attention-controlled, clinical trial to evaluate the physical and psychological effects of Tai Chi for patients suffering from tibiofemoral KOA. Our goal is to compare the safety and effectiveness of Tai Chi with an attention control (wellness education and stretching program) in 40 patients with KOA. (The "single-blind" study design has been decided upon because of the inability to conceal Tai Chi assignment allocation from participants and the instructors in Tai Chi clinical trials. However, all study evaluators will be masked to treatment assignment throughout the duration of the study.)

Outcome parameters compare changes in knee pain, stiffness, and physical function using the well-validated Western Ontario and McMaster University Index (WOMAC), patient and physician global assessments, lower-extremity function, knee proprioception, depression, self-efficacy, social support, health-related quality of life, outcome expectation, adherence and occurrence of adverse events. Outcome measurements are performed at baseline, every week during the intervention period, and on completion of the 12-week program, in addition to the 24 week and 48 week follow-up. Study evaluators (study rheumatologist, study coordinator, exercise physiologist and statistician) are masked to treatment assignment.

The study setting is located in an urban tertiary care academic hospital (Tufts Medical Center) in Boston Massachusetts. The study has received Ethics approval from the Tufts Medical Center/Tufts University Human Investigation Review committee and will be conducted in the Clinical Research Center and Division of Rheumatology at Tufts Medical Center.

### Study population

This study comprises individuals with age > 55 years, Body Mass Index (BMI) ≤ 40 kg/m^2^, and with knee pain on most days of the previous month during at least one of the following activities: walking, going up or down stairs, standing upright, or in bed at night [17]. Furthermore, patients must have joint crepitus, morning stiffness lasting over 30 min. Participants are also required to have positive KOA radiological signs. Radiographic entry criteria are Kellgren and Lawrence (K/L) grade ≥ 2, defined as the presence of osteophytes in the tibiofemoral compartment and/or the patellofemoral compartment, assessed on standing anterior/posterior and lateral views (American College of Rheumatology criteria) [17]. In addition, eligible participants must have a WOMAC pain subscale score (visual analog version) of > 40 (range 0 to 500). Subjects are excluded if they have: 1. prior experience with Tai Chi or other similar types of complementary and alternative medicine such as Qi Gong, yoga or acupuncture; 2. cardiovascular or other severe disease limitations precluding full participation, as determined by the patient's primary care provider; 3. any intra-articular steroid injections in the previous 3 months or reconstructive surgery on the affected knee; 4. any intra-articular Synvisc or Hyalgan injections in the previous 6 months.

Patients can continue routine medications such as non-steroidal anti-inflammatory drugs (NSAIDS) and acetaminophen, and maintain their usual treatment visits with their primary care physician or rheumatologist throughout the study. The investigators record any changes made to treatment but do not change or recommend change in medical therapy.

### Recruitment strategies

Significant gaps in research participation do exist among ethnic minorities and thus limit the generalizability of findings. To ensure adequate enrollment of underrepresented groups, we place advertisements in the media (radio, local television, Internet, SAMPAN – a Chinese newspaper, the Boston Metro and Boston Globe newspapers). We also use the rheumatology clinic patient database at Tufts Medical Center for identifying patients with KOA. For interested respondents, the investigators provide information about the study and administer a brief, scripted interview to determine the caller's eligibility for the trial. This screening poses questions whose predictive values for KOA are known from population-based data. The lists of applicants who screen positive on the telephone interview are provided daily to the trial staff to schedule eligibility visits.

During the 5-month recruitment period, we screened 366 patients from the greater Boston area using telephone interviews from which 62 potential patients were brought into the Clinical Research Center at the Tufts Medical Center for further eligibility screening. Of these, 40 (65%) were eligible after baseline evaluation and randomized to the Tai Chi or attention control group (wellness education and stretching) (See Figure 1). The major reason for ineligibility was the absence of radiographic evidence for KOA.

**Figure 1 F1:**
[figure not shown]
Study flow chart.

### Strategies to maximize adherence

Adherence in clinical research is vital and can determine study quality and the validity of results. In order to maximize adherence, several procedures are performed: 1. Select a population of individuals who are both interested and reliable; 2. Screen patients using a well-designed questionnaire which in our previous studies consistently identified reliable individuals; 3. Discuss the proposed project in detail with each patient, especially the time commitment. A verbal and written commitment will be obtained from all participants, in which they state they will adhere to the program; 4. Schedule the visits at a time that is convenient for both patients and staff; 5. Recruit and assemble sufficient patients for baseline evaluation so that we have a large enough pool of patients to provide replacements if needed; 6. Perform the randomization after the baseline evaluation; 7. Provide friendly personal contact with participants under Institutional Review Board approval; 8. Organize entertaining Tai Chi and education intervention classes. Patients receive useful information that they could not reasonably expect to obtain through regular clinical care.

### Sample size

Our empiric sample size is guided by numbers and outcomes of an RCT conducted at Tufts University that tested an exercise intervention among older adults with KOA [18]. That study enrolled 46 patients and randomized them to either 4-month home-based progressive strength training or an attention control group of similar duration. The results were that the strength training group experienced a 36% decrease in the WOMAC index pain subscale (the primary outcome) compared to an 11% decrease in the attention control group. Thus, the exercise group had a mean change in the WOMAC pain score of -79 (SD = 91), while the control group had a mean change of -20 (SD = 77). Based on those numbers, a sample size of 20 per group and alpha = 0.05, would have power of 60% to detect a between-group difference of -59.0. While we recognize that the study is underpowered for a definitive comparison, we are primarily concerned with gathering preliminary data in order to plan and evaluate this innovative research direction.

### Randomization

Randomization assignments are made using computer-generated random numbers to randomize permuted blocks of size 2 and 4 so that each block is complete. They are provided in a sealed, opaque envelope in two groups of 10 and opened upon the patient's agreement to participate. The block size is randomly assigned to minimize correct prediction of assignments while preserving approximate balance between groups. Specially designed software developed by Tufts Medical Center is used to generate the list of random numbers and treatment assignment. Randomization envelopes are not opened unless a patient meets eligibility criteria and completes the informed consent and baseline assessment. All study envelopes are saved in the individual patient's study notebook. The statistician (CS) closely supervises the preparation process with treatment assignment packets being prepared and checked on specific days. The maximum period between screening and randomization is 3 months.

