#### Knee examination

Knee examination is performed at baseline and during each follow up visit. The study rheumatologist (RK), who is blinded with respect to the patient's treatment assignments, assesses the presence and severity of the knee joint abnormalities relevant to KOA. The knee examination components were selected based on recent data demonstrating the potential for reproducibility across examiners [27]. The study rheumatologist examines for swelling and tenderness of the knee joint and asks each subject to rate pain on a scale of none, mild, moderate or severe. The examination sequence is as follows: 1. Palpate study knee joint swelling (bulge sign, balloon test and patellar tap); 2. Palpate for patella tendon tenderness; 3. Palpate for patella tenderness; 4. Palpate for anserine bursa tenderness; 5. Palpate for popliteal space tenderness; 6. Rate pain in the knee/knee joint when limb is in motion; 7. Scale the general crepitus sign as none, fine or coarse; 8. Palpate for tibiofemoral tenderness laterally; 9. Palpate for tibiofemoral tenderness medially. Evidence of inflammation (e.g. joint effusion), joint deformity, and joint contractures will also be noted. Assessment of the patient's global status is also performed.

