#### Adherence

Participants' attendance is monitored during each session for 12 weeks for both interventions via signing of attendance sheets. Patients are also asked to maintain daily Tai Chi or stretching exercise activity logs during the 12 week intervention and are encouraged with phone calls from the research staff to continue throughout the follow up period. At the 24 and 48 week visit, the research staff will ask about the average number of times per week and the number of minutes per session the subject practices at home.

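### The statistician is declared masked yet supervises preparation of the assignment packets, and envelopes go into patient notebooks: masking is contradicted as written for the statistician and unprotected for the other evaluators

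*Protocol article*

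**What the plan says.** The Study design section of the protocol article calls the trial single-blind, because neither participants nor instructors can be kept unaware of the group. It then makes two statements about everyone else: "all study evaluators will be masked to treatment assignment throughout the duration of the study", and "Study evaluators (study rheumatologist, study coordinator, exercise physiologist and statistician) are masked to treatment assignment". The Knee examination section repeats the claim for the rheumatologist, "who is blinded with respect to the patient's treatment assignments".

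The Randomization section describes how assignments were handled:

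- On generation: "Specially designed software developed by Tufts Medical Center is used to generate the list of random numbers and treatment assignment".
- On concealment: "They are provided in a sealed, opaque envelope in two groups of 10 and opened upon the patient's agreement to participate".
- On oversight, the statistician "closely supervises the preparation process with treatment assignment packets being prepared and checked on specific days".
- On storage: "All study envelopes are saved in the individual patient's study notebook".

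The article does not say who ran the software, who held the list, who opened the envelopes, whether the statistician saw their content, or who could read the notebooks.

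**The concern.** Masking of evaluators and analyst is the only masking this trial claims, so the claim should match the procedures. Here the person named as masked also oversees the step at which assignments are put into packets. The document that reveals each patient's group is then stored in that patient's own record.

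Two things are at stake. The first is analysis. The Discussion says that all 40 patients have finished follow-up and that analysis is still to come, while the Statistical Analysis section foresees single time points, longitudinal analyses, completer analyses and an exploratory knee-based model. An analyst who knows the allocation can be influenced in such choices.

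The second is assessment at weeks 12, 24 and 48. The physician global score, range of motion, proprioception and the performance tests depend on an examiner, and an examiner aware of the group may rate or encourage differently.

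**Working it through.** No figure in the plan depends on this point. The only design calculation, 60% power with 20 per group, does not involve masking. The check is therefore a comparison of the text, role by role.

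**Statistician.**
1. Study design: masked, for the whole study.
2. Randomization: closely supervises the preparation of the packets, which are prepared and checked on set days.
3. Checking an assignment packet normally means comparing its content with the list, so close supervision of that work normally gives access to assignments.
4. A safeguard could reconcile the two statements: a separate unmasked statistician, an independent preparer, or a coded list. The article describes none. It speaks of a single statistician throughout, including the one who breaks ties when choosing the study knee.
5. Result: statements 1 and 2 conflict as written.

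The study-knee task itself adds little. It is a random draw described within the baseline assessment, and envelopes are opened only after baseline.

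**Coordinator, rheumatologist, exercise physiologist.**
1. Study design: masked, for the whole study.
2. Randomization: envelopes are opened once eligibility, consent and baseline are complete, and all are kept in the patient's notebook. For a randomized patient the stored envelope is most naturally the opened one, although the storage sentence does not say so.
3. Study staff could be expected to handle a patient notebook at visits, but the article does not say who had access.
4. Result: a plausible route to the assignment, with no barrier described. This is a risk, not a contradiction.

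**Which outcomes are exposed.**
1. The primary outcome is change in WOMAC pain from baseline to week 12. The WOMAC is self-reported by participants who know their group, so masking of examiners or statistician does not protect its collection.
2. Masking of the statistician bears on how that outcome and the others are analysed.
3. Masking of the other three roles bears on the assessor-rated secondary outcomes at three post-baseline visits.

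**Extent.** One of the four named roles is contradicted as written and three are exposed to an unprotected risk. The ceiling is all 40 assignments (20 + 20), and nothing in the document says how many, if any, were seen.

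**The case against.** A reader might infer that masking failed. The document does not support that. Supervising a process does not prove that the statistician saw or kept the assignments. The sentence on checking is passive and does not say who checked. The list came from software, and the assignments went into sealed, opaque envelopes. Nothing says that any evaluator read a notebook, and the rheumatologist's blinding is stated a second time. All of this stands, and it limits the point to a conflict and a risk.

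A reader might also infer that adherence questions revealed the group, because at weeks 24 and 48 "the research staff will ask about the average number of times per week and the number of minutes per session the subject practices at home", and staff under the same label help with the balance and walking tests. This is not supported either. The label is generic, the questions concern frequency and duration, and both groups were told to practise at home for at least 20 minutes a day. The answers need not reveal the group, and nothing shows that the questioners were the masked evaluators.

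The primary endpoint and the intention-to-treat principle are already fixed, so the room for analyst influence is narrower than the list of planned analyses suggests. That also stands, although how the remaining analyses are chosen and presented can still be affected.

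Finally, custody of envelopes and access to notebooks are details that a journal article may leave to the full protocol. That is a fair reason not to treat the silence as a fault in itself. It does not remove the conflict about the statistician, because the article asserts both sides of it.

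**Conclusion.** The point holds in limited form. The statistician's masking is contradicted by the described procedure. Masking of the coordinator, rheumatologist and exercise physiologist is claimed without protection against one visible route, the envelope in the notebook. The stronger conclusion, that any of the four was in fact unmasked, is not shown.

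The point bears on analysis decisions and assessor-rated secondary outcomes. It does not bear on collection of the self-reported primary outcome. The size of any bias cannot be derived from the document.

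The conclusion rests on three assumptions: the statistician who supervised the packets is the one listed as masked, the stored envelopes are the opened ones, and no safeguard exists that the article leaves out. If the full protocol shows a separate unmasked statistician or restricted notebooks, the matter reduces to a wording correction.

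**What to change.** Reconcile the Study design and Randomization sections in one of two ways:

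- **Keep the claim and support it.** Give the analysing statistician only data labelled A and B until the primary model is locked. Existing staff with no assessment or analysis role hold the allocation list. If the present statistician already has access, someone without access should carry out the analysis to that point.
- **Drop the claim.** Remove the statistician from the list of masked roles and say so in the report.

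Keep opened envelopes in a central file, apart from the notebooks used at assessments. Because follow-up is complete, this can no longer prevent exposure at the visits; it serves any further use of the notebooks and the later trials this study is meant to inform. For this trial, report who generated, held and checked the list and who could open the notebooks, and limit the masking statement to what those facts support.

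The cost is a coded dataset, a filing rule and a few sentences in the report. No additional staff are needed, unless the present statistician has had access and no colleague without it is at hand.
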